#### **D6.4 *Testing Hypotheses and Theoretical Models:***

**D6.4a *Latent growth modeling (LGM):*** Intervention researchers have begun to examine models that can detect differences between individuals in longitudinal rates of behavioral change. We will, therefore, use growth curve modeling to analyze our data, as they will allow us to examine predictors of change within, as well as across, individuals over time. In addition to standard linear models of growth, a variety of non-linear models (e.g., quadratic, logarithmic, non-parametric) will also be tested. Assumptions of homoscedasticity of residuals will be tested explicitly. After careful examination of the missingness mechanism (Schafer, 1997; Schafer & Graham, 2002), software that can accommodate missing data, such as HLM, AMOS, LISREL, or Mplus, will be used to estimate model parameters. This growth curve model allows for differences between individuals in rates of change over time. Because we are interested primarily in assessing differences at follow-up, the intercept will be centered around post-test or follow-up depending on the specific hypothesis being tested. Based on Muthén and Curran's (1997) results, our power to detect effects sizes of .2 or greater with an alpha of .05 is expected to exceed .8 with this sample size and a relatively balanced design. Estimates with ANCOVA also suggest power to detect significant differences at this level (Rausch, Maxwell, & Kelley, 2003).

Several important issues must be considered that, due to space limitations, cannot be addressed in detail. First, research on LGM with substance use suggests that an S-shaped logistic function may be more appropriate than a linear function (see McArdle, 2002; Spoth, Redmond, Shin, & Azevedo, 2004). Second, as in any intervention study, the missing data mechanism must be integrated into the analytic plan while considering patterns commonly observed in a mixture model. For example, the groups may include participants engaging in low levels of substance use at the beginning of the study who do not increase their use, early initiators who maintain their initial use levels, participants who increase use gradually, and so forth. We will address this issue by integrating the missing data mechanism (e.g., Hedeker & Gibbons, 1997) and the various types of trajectories (e.g., Muthén, 1997; Nagin & Tremblay, 2001) into a single integrated analytic framework. In addition to this approach, we will also estimate random effects Tobit models using Stata. This allows for the censoring of substance use at 0. Nonusers may vary in the strength of their avoidance of usage; some may be seriously considering trying a particular substance whereas others have no intention whatsoever of using. We will evaluate these models in comparison with others appropriate for our outcome measures, including zero-inflated Poisson and negative binomial models (Long, 2003).

*D6.4b. Aim 5: Testing mediational paths in the causative model:* With our proposed sample size and design, we should be able to detect an effect size of .20 or greater 80% of the time with an alpha of .05 (Muthén & Curran, 1997). The sample is larger than needed for detection of significant group differences because we also plan to contribute to theory development by testing mediational pathways; proposing a framework for exploratory analyses; examining moderators of change; comparing various developmental trajectories; and identifying all relevant individual, intervention-related, and time-varying covariates in our analyses.

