### **D.8.2. Analyses for Aims 1 and 2: Primary Outcomes**

The primary issue to be addressed in Aims 1 and 2 is SAAF-HS's effectiveness in deterring the onset and escalation of substance use and high-risk sexual behavior across the 18 months separating the pretest and long-term follow-up assessments. A dramatic growth in substance use and high-risk sexual behavior is likely to occur across measurement points, which include the beginning of 10th grade, middle of 10th grade, and beginning of 11th grade. SAAF-HS's impact on each of the outcomes will be examined in three ways: on posttest (middle of 10th grade), on long-term follow-up (beginning of 11th grade), and on growth trajectories. The two single-time-point analyses will be conducted with Structural Equation Modeling (SEM) using the maximum likelihood method and controlling for baseline levels of substance use and high risk-sexual behavior. The first outcome analysis (posttest) identifies reduction in substance use and high risk-sexual behavior; the second (long-term follow-up) will be used for tests of delayed initiation and reduction of substance use and reduction of high-risk sexual behavior. We will explore, in an additional analysis, SAAF-HS's effects on delaying the onset of sexual intercourse. SAAF-HS, however, is likely to have its strongest impact on growth trajectories (Taylor et al., 2000). A baseline growth model with random intercepts and slopes will be established for the attention-control condition. A multigroup analysis will then be conducted, testing the equivalence of growth parameters between the attention-control and the SAAF-HS groups (Byrne, 2001). If the multigroup analyses detect differences between the slopes (rates of growth for substance use or high-risk sexual behavior) of the SAAF-HS and attention-control group, impact statements will be made by examining how the average substance use and sexual risk behavior trajectories change with time.

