### **D.8.6. Statistical Power**

In this section, we discuss statistical power for the models we described previously, including the SAAF–HS intervention’s impact on changes in the slopes of drug use and high-risk sexual behavior and on outcomes at a single point in time. In these calculations, we assume conservatively a 13% loss in data across time, yielding two groups of 250 participants in each condition. For growth models with either continuous or discrete outcomes, we have used power calculations that Brown and colleagues have made available on the internet (<http://psmq.usf.edu/products.html>) to determine the smallest effect size we can detect with 80% power for changes in the slope parameter, assuming linear growth over three time points. When the measurement reliability is 60%, we can achieve 80% power when the ES is 0.1 at posttest and grows to 0.2 at long-term follow-up. For conducting a test at a single time point on a continuous outcome, based on Cohen (1988), we can detect an effect size of 0.25 at 80% for a 0.05 level test, assuming negligible variation based on school. We also have calculated power by taking this factor into account. Based on variability observed in other preventive trials among schools and individuals (Brown and Liao, 1999) the power is 80% to detect an ES of 0.36 and 70% to detect an ES of 0.31 for 0.05 level tests. Thus, we clearly have adequate power to detect a moderate effect for continuous outcomes involving single time points. For a discrete measure at a single time point, such as a comparison of the proportion of individuals who are using a substance, we will be able to detect an odds ratio of at least 1.6 with 80% power using a 0.05 level chi-square test (Fleiss et al., 2003). This odds ratio corresponds to a reduction from 50% users to 38% in the intervention group.

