## AIM

### A. SPECIFIC AIMS

Our sample will consist of 370 families with a high school senior, half of whom will be assigned randomly to a prevention group (SAAF—EAP) and half of whom will be assigned to a control group. Pre-intervention, post-intervention, and follow-up assessments of youths' substance use and secondary outcomes will be conducted with the entire sample. Our specific aims are as follows:

1. To test the hypothesis that rural African American emerging adults randomly assigned to participate in SAAF—EAP, compared to control participants, will demonstrate lower rates of substance use initiation, and that those who already use substances (e.g., cigarettes; alcohol, including binge drinking; marijuana and other illicit substances) will use them less frequently and consume lower quantities, at each follow-up assessment.
2. To test the hypothesis that SAAF—EAP primary caregivers and emerging adults, compared to control participants, will report higher levels of autonomy-promoting parenting and responsiveness in family relationships at each follow-up assessment.

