**D6.3. *Power Analysis:*** As mentioned in Section D1, 690 families will be recruited to allow for an attrition rate of 15%. Power analyses were based on an effect size of .30 (Durlak & Wells, in press). Table 9.4.1 in Cohen (1977) can be used to calculate a necessary sample size of around 150 families per group to detect differences between the prevention and comparison groups with an alpha of .01 and a power of .90 for the dependent measures. For the analyses presented below using structural equation modeling (SEM), we considered both sample size and statistical power issues. The literature on sample size for latent variable structural equation analysis suggests that 150 cases are enough to ensure a reliable estimation of the model (see discussion by Tanaka, 1987). Much of this literature, however, is based on Monte Carlo studies of factor analysis models involving relatively few parameters (e.g., Boomsma, 1982). An alternate perspective is to consider the available sample size relative to the number of parameters that the model is estimating. For example, Bentler (1985) recommends at least 5 cases per parameter. We expect to have a sufficiently large sample to permit testing of the causal models described below. Based on the parameters derived from the research described in Section C, we conducted power analyses using Jöreskog and Sörbom's (1993) LISPOWER program. Our analyses evaluated the model's ability to detect the statistical significance of path coefficients that vary in their "true" magnitude, holding the other parameters in the model constant at values derived from the analyses presented in Section C. These power calculations were significantly different from 0 at  $p < .05$ . We evaluated the statistical power of these models for samples that varied in size from 150 to 170 cases. For the causal paths included in the models discussed in Section C, the power was above .80 for detecting path coefficients of .17 to .20 in absolute magnitude for samples of 150 cases or more. These coefficients correspond to those that Cohen (1988) termed small effects. These results suggest that we will have sufficient power to detect even relatively weak relations among variables.

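### Neither growth model holds pretest means equal across randomised arms or names pretest as a covariate, so baseline information that could raise power may go unused

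*Combined protocol and SAP*

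**What the plan says.** **AIM.** D6.4a makes growth curves the main analysis and puts the interest on differences at follow-up, so "the intercept will be centered around post-test or follow-up depending on the specific hypothesis being tested". It adds that "our power to detect effects sizes of .2 or greater with an alpha of .05 is expected to exceed .8", and then that "Estimates with ANCOVA also suggest power to detect significant differences at this level". ANCOVA appears only in that power remark, not as a planned test. D6.1d plans comparisons of the arms at pretest before the hypotheses are tested, but does not carry pretest into the growth model.

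**SAAF-T.** D.8.2 lists three looks at each outcome: posttest, long-term follow-up and growth trajectories. The two single-time-point analyses control for baseline. For growth, a model with random intercepts and slopes is set up in the control arm, after which "A multigroup analysis will then be conducted, testing the equivalence of growth parameters" between arms. No constraint on pretest means is mentioned, free or equal. The same section expects the programme's strongest effect to be on trajectories. D.8.6 states that, with measurement reliability of 60%, "we can achieve 80% power when the ES is 0.1 at posttest and grows to 0.2 at long-term follow-up".

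Families are randomised individually in both trials (SAAF-T D.1.1, AIM D1.1).

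**The concern.** In a linear growth model where arm predicts both intercept and slope, or in a two-group model with separate intercepts, the arm difference at pretest is estimated unless the analyst fixes it. Moving the time origin to follow-up does not change that; it only makes the intercept contrast the arm difference at follow-up. In a randomised trial the true pretest difference is zero in expectation, so estimating it costs precision that a pretest covariate or an equality constraint would recover.

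At stake is power in the analysis to which both plans give the leading role. There is also a pre-specification gap: an analyst could fit the model with or without the constraint after seeing the data, and the two can differ materially in precision.

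**Working it through.** **Inputs.** AIM A: "Our sample will consist of 370 families with a high school senior", and "half of whom will be assigned to a control group". That is 185 per arm, and 185 × .85 ≈ 157 after the 15% attrition in D6.3. D6.3 itself says that "690 families will be recruited to allow for an attrition rate of 15" per cent, which is 345 per arm, or about 293 after attrition. AIM visits: a 6-week programme, then 3 months, then 9 months, so about 0, 4.5 and 13.5 months (D2). SAAF-T: 250 per arm and effects of 0, .1 and .2 (D.8.6), which is a straight line on times 0, 1, 2. Assumed: two-sided .05, unit variance, compound symmetry with correlation ρ from .3 to .8. No ρ is given for either trial.

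**AIM's stated power.** An unadjusted two-sided comparison at d = .20 gives 48.5% (185 per arm) or 42.5% (157), and 74.8% (345) or 67.8% (293) on the larger sample. With pretest as a covariate the residual variance is 1 − ρ², and .80 needs ρ of at least .73, .78, .35 and .50 respectively. The stated figure cannot be reproduced without knowing ρ and the sample size.

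**Formulas.** The arm contrast at the last visit T has variance 2v/n, and power ≈ Φ(d/√(2v/n) − 1.96). With Sxx = Σ(t − t̄)²:

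- follow-up difference, pretest free: v = ρ + (1 − ρ)[1/3 + (T − t̄)²/Sxx]
- slope × T, pretest free: v = (1 − ρ)T²/Sxx
- linear path, pretest difference zero: v = T²(1 − ρ)/[Σt² − ρ(Σt)²/(1 + 2ρ)]
- pretest difference zero, later visit means unrestricted (or ANCOVA): v = 1 − ρ²

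**AIM at ρ = .6.** t̄ = 6, Sxx = 94.5, Σt² = 202.5, Σt = 18.

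- Free: v = .6 + .4(.3333 + 56.25/94.5) = .971, power 43.6%.
- Equal, linear: v = 182.25 × .4/(202.5 − .6 × 324/2.2) = .639, power 60.2%.
- Equal, unrestricted later means: v = .640, power 60.1%.

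**SAAF-T at ρ = .6.** Sxx = 2, Σt² = 5, Σt = 3.

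- Free slope: v = .4 × 4/2 = .800, power 70.5%.
- Equal pretest: v = 4 × .4/(5 − .6 × 9/2.2) = .629, power 80.5%.

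**Over the range of ρ** (power in %, final effect .20):

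| ρ | AIM follow-up, free | AIM, equal (linear) | Gain | SAAF-T slope, free | SAAF-T slope, equal | Gain |
|---|---|---|---|---|---|---|
| .3 | 44.4 | 46.3 | 1.9 | 47.2 | 68.2 | 21.0 |
| .4 | 44.1 | 49.0 | 4.9 | 53.2 | 70.5 | 17.3 |
| .5 | 43.8 | 53.4 | 9.6 | 60.9 | 74.6 | 13.7 |
| .6 | 43.6 | 60.2 | 16.6 | 70.5 | 80.5 | 10.0 |
| .7 | 43.3 | 70.2 | 26.9 | 82.3 | 88.2 | 5.9 |
| .8 | 43.0 | 84.5 | 41.5 | 94.2 | 96.2 | 2.0 |

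The two gains run in opposite directions because the free slope test already uses pretest as its first point, while the free follow-up contrast hardly uses it at all.

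**Sensitivity.**

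- AIM at 293 per arm: follow-up gain of about 2 to 30 points (69.0% to 85.7% at .6).
- AIM slope test at 157 per arm: about 3 to 13 points.
- SAAF-T at 500 × .87/2 = 217.5 per arm: 64.5% to 74.9% at .6.
- Random slopes with reliability .6: about 7 to 15 points for the AIM follow-up contrast and 5 to 9 for the SAAF-T slope, depending on the slope variance assumed.

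**The case against.** The strongest reply is that this is silence, not a mis-specified model. The AIM sentence sets a time origin and nothing else, and SAAF-T's test of growth parameters could begin by equating intercepts. That stands: a reader might infer that the plans allow pretest means to differ, but no text says so. The point is that neither plan rules it out, and the usual fit leaves the difference free.

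Second, baseline is not ignored. Two of SAAF-T's three outcome analyses control for it, the slope test uses pretest data, and AIM D6.4b speaks generally of identifying relevant covariates. This also stands, but none of it settles the growth contrast.

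Third, compound symmetry has no random slopes, whereas both plans allow individual rates of change. Random slopes shrink the SAAF-T slope gain to about 5 to 9 points but do not remove it.

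Fourth, fixing the pretest difference at zero on a straight line ties the follow-up effect to linearity, which both plans question. That is a fair objection to the linear version only. With the later means unrestricted, AIM power at ρ = .5, .6 and .7 is 53.4%, 60.1% and 69.9%, against 53.4%, 60.2% and 70.2% on a line.

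Last, the figures are for continuous outcomes. No gain has been worked out for the two-part, zero-inflated, Tobit or event-history models.

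**Conclusion.** The concern holds as an efficiency and pre-specification gap, not a validity error. Neither growth analysis commits to using the fact that randomised arms share a pretest mean. As ordinarily fitted, AIM's follow-up contrast has power of about 43% to 44% for d = .20 at 157 per arm whatever the correlation, close to the unadjusted 42.5%. Adjustment raised power in every case tried, by about 2 to 42 points for AIM at follow-up and about 2 to 21 for the SAAF-T slope under compound symmetry.

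Two stronger readings are not supported. A reader might quote a single gain of 10 to 20 points; for the AIM follow-up contrast that holds only for correlations from about .5 to the low .6s, and the documents give no correlation. A reader might also infer from the 80.5% that SAAF-T's stated 80% assumed equal pretest means. That match rests on reading a measurement reliability of .60 as a compound-symmetric correlation between visits. At .7 the free model already gives 82.3%, and the calculator used is not in the documents.

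**What to change.** **AIM D6.4a:** test the arm difference at post-test or follow-up with pretest as a covariate, or with the pretest arm difference fixed at zero and the later visit means not forced onto a line.

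**SAAF-T D.8.2:** hold the time-0 means equal across arms in the multigroup model before testing slopes.

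**Both:** apply the same baseline adjustment in the non-Gaussian models where feasible, and state the pretest-to-follow-up correlation behind each growth power figure. AIM should also say whether 370 or 690 families underlie its figure.

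The cost is a sentence and a model constraint or covariate in each plan, plus a rerun of the power calculation. No new data or families are needed.
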